### Criteria for discontinuing or modifying allocated interventions {11b}

Discontinuation of the allocated intervention is possible after a participant withdraws from the intervention and/or trial or based on clinical judgement by the intervention facilitator, e.g. when a participant’s mental health deteriorates and is not advised by their clinician to continue.

### Strategies to improve adherence to interventions {11c}

Adherence to the intervention is facilitated in several ways. Firstly, potential participants are informed of the dates, times and location of the intervention sessions before they decide to participate. Potential issues around attendance are discussed and resolved, i.e. the trial covers childcare and transportation costs for the face-to-face sessions and a tablet with data can be arranged for the virtual sessions. Facilitators are encouraged to schedule pre-group individual calls with everyone assigned to their group and to reach out to anyone who misses a session to allow a smooth re-entry in the group.

Also, the trial explores treatment fidelity of COS-P within the trial. Each facilitator delivering COS-P within the trial will be trained in its delivery by accredited COS International trainers and are given a clear group delivery manual to follow. Additionally, all facilitators undertake 20 h of fidelity coaching. The fidelity coaching includes 10, 2-h coaching sessions with a supervisor from COS International. Lastly, all facilitators will receive supervision from expert therapists at their PMHS trained in parenting interventions and/or COS-P.

Fidelity of delivery will be checked by recording all ten sessions of one full group for each intervener. A randomly selected 20% of recorded videos will be coded for fidelity to the manual. A criterion of 75% adherence to the COS-P manual will be used to ensure that the treatment administered meets the standards of fidelity required for the trial.

Additionally, attendance to the intervention sessions is monitored and 6/10 sessions is considered a clinical dose. When participants miss a session, an individual catch-up session is offered to help them re-enter the group and this does not itself constitute attendance of an intervention session.

### Relevant concomitant care permitted or prohibited during the trial {11d}

All participants receive TAU from their PMHS and COS-P cannot be offered to participants in the control arm.

### Provisions for post-trial care {30}

No provisions for post-trial care are in place. Additionally, there is no anticipated harm and compensation relating to harm for trial participation.

### Outcomes {12}

#### Outcome measures—quantitative data collection

The primary outcome measure is the Clinical Outcomes in Routine Evaluation – Outcome Measure (CORE-OM; [33]), included in all trial assessments. The CORE-OM is a 34-item measure of psychological distress and is one of the most widely used outcome measures in secondary care mental health services.

Secondary outcome measures exploring parent-infant bonding, experienced childhood maltreatment, emotion regulation, parenting quality, health-related quality of life, health service use, child development and attachment style, adverse events, and COS-P cost-effectiveness will also be completed throughout the trial. Details on these measures are provided in Additional File 4.

#### Outcome measures—qualitative data collection

The qualitative data will explore acceptability and accessibility of COS-P and possible mechanisms of change, from the perspectives of parent participants in the intervention arm and NHS staff who are involved in the delivery of COS-P within the trial. This will be achieved through surveys, interviews and focus groups as outlined later.

### Participant timeline {13}

Please see Additional File 1 for details relating to the participant timeline.

### Sample size {14}

A change in CORE-OM of 5 has been proposed as a meaningful improvement and a reliable change that exceeds that which might be expected by chance [9]. In a 2009 trial, Morrell et al. [34] reported that in a sample of birthing parents with Edinburgh Postnatal Depression Scale (EPDS) scores ≥ 12 (i.e. birthing parents with probable perinatal mental health difficulties), the mean score on the CORE-OM had a standard deviation of 0.5. A change in total score of 5 equates to an average mean item change of 0.147. The CORE-OM total change score we are using was strongly endorsed by our EbE panel as being meaningful. A between measurements within subject correlation of 0.35 were estimated, from unpublished clinical audit data on 71 birthing parents in a specialist community perinatal mental health service.

We choose to use a 2:1 ratio to randomise to increase motivation of participants to take part in the trial due to the perceived benefit of the intervention, and with consideration to the practicality of filling up recruitment blocks in a timely manner, as we need at least 4 participants within each COS-P group.

With 104 parents in the control arm and 208 parents (*N* = 312) in the intervention arm, we will have 90% power to detect a minimally clinically important average mean item change of 0.147, assuming a *SD* of 0.5, three repeated measurements with a correlation of 0.35 and using a 5% significance threshold. Previous small trials have reported 15–20% missing at follow-up [20, 21] by the end of the trial. In the current trial, participants will be rigorously followed up and those who have at least one post-randomisation measurement will be included in the analysis. We therefore assume it is reasonable to obtain one post-randomisation measurement of the primary outcome in at least 90% and therefore factor in 10% missing. As the intervention is delivered in groups, there is potential for clustering of the outcomes in the active arm. We do not have reliable data to inform us what the intra-cluster correlation (ICC) coefficient in this context is. However, even if the ICC were large (> 0.05), the intervention group size is small so the effect will be limited. It is not expected this clustering will greatly affect the results. To protect against any potential effect in the absence of information, we inflated the sample size by an additional 5% to take into account the potential for one-arm clustering. Taking into account the potential for clustering (5%) and missing data (10%), we will aim to recruit a total of 369 birthing parents (*n* = 246 and *n* = 123 per arm). This was calculated using the time-averaged difference test in the PASS statistical software.

For the embedded qualitative component, we have estimated interviewing 20–30 completers, which is consistent with other HTA-funded process evaluations (e.g. ISRCTN12655391, ISRCTN34701576) and aim to interview all non-completers. The total sample size will be guided by principles of data saturation concerning meaning [35] and with emphasis on data quality. It is therefore not possible to determine the exact sample size in advance. Focus groups with staff will use total population sampling, i.e. inviting all members of those groups.

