**Methods:**

COSI is an individually randomised, single-blind parallel arm controlled trial with an embedded internal pilot aiming to recruit 369 participants in a 2:1 ratio (intervention: TAU). Participants will be recruited from ten NHS community perinatal mental health services in England and screened based on clinical levels of both mental health symptoms (average CORE-OM score ≥ 1.1) and postnatal bonding difficulties (total PBQ score ≥ 12). This trial has 90% power to detect a MCID of 5 points on the CORE-OM. Primary and secondary outcomes will be measured at baseline, 3, 7 and 12 months after baseline. Service use and quality of life measures will also be collected alongside a process evaluation of parents’ and interveners’ views and experiences.

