#### Primary analyses

For the primary analysis, we will use a mixed effects linear regression model to estimate the mean difference in CORE-OM between arms over 3-, 7- and 12-month follow-up trial assessments and a Bayesian mixed effects linear regression model using vague priors. From the Bayesian model, we will obtain the posterior probability of the intervention being superior to TAU, as well as the posterior probability of treatment effect exceeding the pre-specified Minimal Clinically Important Difference (MCID) of 5 points in the CORE-OM. In the mixed effects linear regression model, participants and recruitment cohort (in the intervention arm to account for group clustering in one arm) will be included as random intercepts. Fixed effects in the model will be intervention arm, site, and baseline CORE-OM, infant sex, infant age and infant first born status [36]. The mean difference in CORE-OM over 3-, 7- and 12-month follow-up trial assessments will be reported, with accompanying 95% confidence intervals, and *p*-value will be presented.

A Bayesian mixed effects linear regression model will be fitted and follows the same form as the frequentist mixed effects linear regression model described above. We will use vague (large variance) normal priors for regression coefficients and inverse-gamma priors for the error variance and for the variance of random intercepts which have been chosen to be uninformative. Model convergence will be investigated for the parameters of primary interest (specifically the treatment effect estimate) using graphical diagnostics. The intervention effect will also be estimated at the 3-, 7- and 12-month follow-up trial assessments using a Bayesian mixed effects linear regression model with a model including time point and adding a time-by-intervention arm interaction.

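### The 5-point CORE-OM threshold, read as a 34-item total (0.147 per item), cannot be the reliable change the plan says it is, and the posterior benefit threshold names no scale

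*Protocol article*

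**What the plan says.** Sample size {14} opens by saying of a CORE-OM change of 5 that it "has been proposed as a meaningful improvement and a reliable change that exceeds that which might be expected by chance", citing reference 9. That sentence does not say on which CORE-OM scale the 5 is measured. The conversion comes two sentences later: "A change in total score of 5 equates to an average mean item change of 0.147". The divisor is the item count given under Outcomes {12}: "The CORE-OM is a 34-item measure of psychological distress". The same section reports, from an earlier trial, that "the mean score on the CORE-OM had a standard deviation of 0.5", and adds that the Expert by Experience panel strongly endorsed the total change score as meaningful.

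The figure is used in three places:

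- Sample size {14} powers the trial for an item-mean difference of 0.147.
- The Abstract states: "This trial has 90% power to detect a MCID of 5 points on the CORE-OM".
- Primary analyses plans to report the "posterior probability of treatment effect exceeding the pre-specified Minimal Clinically Important Difference (MCID) of 5 points in the CORE-OM".

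Neither of the last two says whether the points are total points. Eligibility, the SD and the powered difference are all expressed as item means.

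**The concern.** The plan makes two statements about one number: that 5 is a change beyond what chance would produce, and that it is 5 points on a sum of 34 items. Whether a change is reliable depends on the SD and on the reliability of the score. On the stated SD, 0.147 per item is small, so the two statements look incompatible. If they are, either the reliable-change label is wrong or the 5 was defined on a different scale and converted wrongly.

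The number is more than background to the sample size. It is the pre-specified line above which the Bayesian model will describe the benefit as clinically important. If that line sits on the wrong scale, the trial could report a high probability of an important benefit for an effect that its own source would not call important.

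**Working it through.** **Inputs from the documents (Sample size {14}, Outcomes {12}).** 34 items; threshold 5; item-mean SD 0.5; 104 control and 208 intervention; "three repeated measurements with a correlation of 0.35 and using a 5% significance threshold". A two-sided test is assumed because it reproduces the stated power.

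**Step 1: the plan's own figures.**
- Conversion: 5/34 = 0.147. In SD units, 0.147/0.5 = 0.29.
- SD of the mean of three measurements: 0.5 × √[(1 + 2 × 0.35)/3] = 0.376.
- Standard error of the arm difference: 0.376 × √(1/104 + 1/208) = 0.0452.
- Power: Φ(0.147/0.0452 − 1.96) = Φ(1.29) = 90.2%.

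The division and the 90% power both reproduce.

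**Step 2: reliability needed for 0.147 to be a reliable change.** The smallest individual change beyond measurement error at 95% is 1.96 × SD × √[2(1 − r)], where r is reliability. Setting this to 0.147 with SD 0.5 gives

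r = 1 − (0.147/(1.96 × 0.5))²/2 = 1 − 0.0225/2 = 0.989.

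A looser criterion changes little: r must be 0.984 at 90% and 0.974 at 80%.

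**Step 3: reliable change at plausible reliabilities.** The documents give no reliability, so these values are assumed.

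| Assumed r | Reliable change per item | On the 34-item total | Chance that an unchanged person improves by 5 or more total points |
|---|---|---|---|
| 0.80 | 0.62 | 21.1 | 32% |
| 0.90 | 0.44 | 14.9 | 26% |
| 0.95 | 0.31 | 10.5 | 18% |

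The last column is 1 − Φ(0.147/(0.5 × √[2(1 − r)])). The correlation of 0.35 in the plan is between visits and is not a reliability coefficient, so it is not used here.

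The result does not hang on the exact SD. Even at r = 0.95, 0.147 would be a reliable change only if the SD were 0.147/(1.96 × √0.10) = 0.24, less than half the stated value.

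**Step 4: how much the threshold matters.** Take an observed benefit of 0.20 per item, vague priors and the standard error of 0.0452 (ignoring clustering and baseline adjustment).
- Probability of exceeding 0.147: Φ((0.20 − 0.147)/0.0452) = Φ(1.17) = 0.88.
- Probability of exceeding 0.31: Φ((0.20 − 0.31)/0.0452) = Φ(−2.43), below 0.01.

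The same data would support opposite statements, depending on where the threshold is put.

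**Step 5: power if the threshold is larger.** With 104/208, power is 99.3% at 0.20 and above 99.99% at 0.30.

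**The case against.** The strongest reply is that a minimal important difference between arms need not equal a reliable change in one person. The formula in Step 2 concerns measurement error in an individual, whereas the posterior threshold applies to a difference in arm means averaged over three visits. The panel's endorsement is separate support for the word meaningful. Both points stand. They keep 0.147 usable as a target difference, but they do not rescue reliable change, which the plan itself offers as a justification.

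It is also fair to say that the SD alone proves nothing without a reliability, and that none is given. The conclusion does depend on reliability, but it holds for any value below about 0.989.

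The omission of the word total in the Abstract and Primary analyses can be called a wording gap, since Sample size {14} supplies the conversion and the analysis plan, not shown here, may state the scale. That is reasonable. A reader might object that a literal 5 on item means would be ten SDs (5/0.5), but nothing suggests the analysis would be run that way.

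Three stronger readings are tempting and are not supported:

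- **The 90% power is wrong or the trial is underpowered.** It is not: the power reproduces, and a larger important difference would only raise it.
- **The cited 5 belongs to a score of ten times the item mean, so the threshold should be 0.50.** On that assumption a reliability of 0.87 would make it a reliable change, but the documents mention no such scale, and the source is not shown.
- **The threshold is two to four times too small.** That compares 0.147 with 0.31 to 0.62, and so assumes both a reliability and that the group-level threshold must equal an individual reliable change.

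**Conclusion.** The concern holds in a limited form. On the 34-item total, 5 points is 0.147 per item or 0.29 SD, and the claim that this is a reliable change conflicts with the plan's own SD unless reliability is about 0.989. Under assumed reliabilities of 0.80 to 0.95, a reliable change would be 21 to 10.5 total points. The scale of the cited 5 is therefore in doubt but cannot be determined from the documents.

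What is affected is the justification of the threshold and the meaning of one pre-specified posterior probability. The 104/208 design, the target of 369, the 90% power for 0.147 and the frequentist estimate with its p-value do not change. The conclusion assumes that the stated SD of 0.5 applies and uses the usual 95% criterion; relaxing the criterion to 80% still requires a reliability of 0.974.

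**What to change.** Before data lock, and in the detailed analysis plan that the article promises by then:

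1. Check the cited source and record the CORE-OM scale on which the 5 was defined.
2. State the analysis scale and the threshold in the same units wherever the 5 appears: Abstract, Sample size {14} and Primary analyses.
3. Remove reliable change as the justification for 0.147, and describe 0.147 as the panel-endorsed target difference used for power.
4. If the source scale is not the 34-item total, also report the posterior probability at the correctly converted threshold, and base any statement about the MCID on that one. If it is the total, no second threshold is needed.

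The cost is a source check and some re-wording, with no extra participants and no new power calculation. The downside is that the statement about exceeding the MCID may become less favourable. Settling this before results are known avoids the appearance of a threshold chosen afterwards.

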### Recruitment {15}

We aim to recruit a total of 369 birthing parents in up to seven, 4-week recruitment blocks in each of the sites over a 20-month period. Based on this, we have calculated that we will need to screen 1262 birthing parents during this time, which draws from some of the most conservative data in previous trials and published studies on recruitment (65% of birthing parents consenting to be screened, 75% meeting the screening criteria and 60% consenting to be randomised across the study period) [20, 21, 36].

## Assignment of interventions: allocation

### Sequence generation {16a}

At the end of each recruitment block, participants will be randomly allocated to one arm of the trial (2:1, intervention:TAU stratification) using a web-based randomisation system using computer-generated random list stratified by trial site and recruitment cohort. All researchers collecting baseline and follow-up data, as well as assessors of outcome measures, will be blinded to group allocation.

### Concealment mechanism {16b}

The randomization list is concealed using an online web-based randomisation system integrated into the Electronic Data Capture. Participants are entered into the system and consented prior to allocation being revealed.

### Implementation {16c}

The allocation sequence is generated by the trial statistician. Participants are enrolled by the study team and assigned to the intervention by the trial manager using the EDC system.

## Assignment of interventions: blinding

### Who will be blinded {17a}

Study team members collecting quantitative data and study quantitative outcome assessors are blinded to the intervention. It is not possible to blind the analysts due to the 2:1 allocation ratio.

### Procedure for unblinding if needed {17b}

If study team members are unblinded, this will be recorded via a protocol deviation form within the trial database. The unblinded team member will complete no further data collection or outcome assessments with that participant for the duration of the trial. As participants are not blinded to allocation, there is no requirement to have a facility available for unblinding participants.

## Data collection and management

### Plans for assessment and collection of outcomes {18a}

#### Data collection and management—quantitative data collection

Participants are offered the possibility of face-to-face (e.g. at home) and virtual trial assessments (via Microsoft Teams) at baseline, 3-month and 7-month follow-up assessments. Baseline trial assessments take place prior to randomisation and the first COS-P session. The trial aims to have no more than 4 weeks between randomisation and the first COS-P group session. As the 12-month follow-up assessment includes the Strange Situation Procedure (SSP; [37]) used for assessing attachment security of the child, this trial assessment takes place in person at a venue local to the participant. Please see Table 2 for further details regarding the data collection schedule. Apart from the video-recorded parent–child interaction and the SSP, participants are given the choice to self-complete the measures online, or to complete them together with a member of the research team. Details on all study measures are provided in Additional File 4.

**Table 2 Tab2:** COSI study data collection schedule

	**Screening**	**Baseline**	**COS-P group (intervention arm only)**	**3-month f/u**	**7-month f/u**	**12-month f/u**
Informed consent	X	X				
CORE-10	X					
Inclusion and exclusion criteria		X				
Demographics		X				
Randomisation		X				
CORE-OM		X		X	X	X
PBQ	X	X		X	X	X
CTQ-SF		X				
DERS		X		X	X	X
ASQ-SE		X		X	X	X
ASQ-3		X		X	X	X
Sensitivity scales		X		X	X	X
CSRI		X		X	X	X
EQ-5D-5L		X		X	X	X
CORE-6D		X		X	X	X
SSP						X
Adverse events		X		X	X	X
Short experience survey			X			
Qualitative interviews			X			

### Data collection and management—qualitative data collection

Qualitative data collection is completed shortly after the 3-month follow-up of the trial. All participants in the intervention arm of the trial are asked to share their views and experiences using survey materials designed for the trial in collaboration with the EbE panel; to explore the acceptability and accessibility of COS-P, see Additional File 5. The survey will additionally provide a sampling framework for the interviews with completers (i.e. those who attend at least six sessions), using maximum variation sampling [38] to ensure that parents with a wide range of background characteristics are included (e.g. diversity in relation to ethnicity, relationship status, age, parity, infant age) and from across sites and recruitment blocks. All non-completers (i.e. those who begin COS-P but attend fewer than six sessions) are invited to be interviewed.

Interviews are approximately 1 h long and follow a topic guide based on the trial aims (see Additional File 6). In addition to this, focus groups with NHS Staff members involved in the delivery of COS-P within the trial are completed. These focus groups explore staff views of the intervention and experiences of delivery, either through direct facilitation or supervision of staff involved in facilitation. Focus groups are 1.5–2 h long and follow a pre-determined topic guide (see Additional File 7). Any facilitators who leave the trial prior to a focus group having taken place will be offered individual interview. Both the interviews and focus groups will be audio/audio-visually recorded and transcribed verbatim.

### Plans to promote participant retention and complete follow-up {18b}

It is intended that newsletters regarding the trial will be shared with participants in the study to promote engagement. Parent participants also receive a £10 voucher per trial assessment as reimbursement for their time. An additional £20 voucher will be provided as reimbursement for parent participants who take part in an interview for the qualitative assessment.

If a participant chooses to withdraw from all study procedures, no further outcome data will be collected. Any information regarding the reason for the withdrawal will be recorded in the trial database. If a participant chooses to withdraw from the study intervention only, all future follow-up visits will be completed as per the study protocol.

